## Methods/design

### Design

The present trial is a single-center experimental observational study with a matched control group. An experimental group of children and adolescents with diagnosed anxiety disorder according to the criteria of the Diagnostic and Statistical Manual of Mental Disorders-IV (DSM-IV) and International Statistical Classification of Diseases and Related Health Problems-10 (ICD-10) will be compared to a matched control group of same-aged healthy children and adolescents. The procedure applies to both groups. Psychometric assessment, hormone assay, as well as physiological measurements (heart rate) will be investigated. The study protocol conforms to the Standard Protocol Items: Recommendations for interventional Trials (SPIRIT) checklist (See Additional file 1).

### Setting and recruitment

The study will be conducted at the Clinic for Child and Adolescent Psychiatry, Psychosomatics and Psychotherapy at the University of Regensburg, Germany. The aim is to include N = 64 children and adolescents aged 11–18 years. 32 patients with anxiety disorder and 32 healthy controls will be recruited from the region of Regensburg. Potential participants will be approached through the consecutive admission to the in- or outpatient clinic department, study flyers, via email distribution to colleagues and advertisements in the pediatric and psychiatric services. Upon showing interest in study participation, the potential participant will be contacted and initially screened for eligibility by telephone or personal conversation.

### Eligibility criteria

All participants and their legal guardians have to provide a sufficient understanding of the German language and a declaration of informed consent before taking part in the study. The study protocol has been approved by the ethical committee of the University of Regensburg. The experimental group will consist of children and adolescents meeting the criteria of an anxiety disorder according to the classification systems DSM-IV and ICD-10. Included diagnoses are Agoraphobia (ICD-10 F40.0) with/without panic disorder (F40.00, F40.01), social phobia (F40.1), panic disorder (F41.0), generalized anxiety disorder (F41.1), separation anxiety disorder of childhood (F93.0) as well as social (F93.2) and generalized (F93.80) anxiety disorder of childhood. The categorical diagnoses of diseases will be assessed using the semi-structured diagnostic interview M.I.N.I-KID 6.0 [44]. Anxiety-questionnaires (BAI [45], BDI-II [46], STAI [47], SPAIK [48], SCARED-D [49, 50]) will be administered to measure the symptomatology of anxiety dimensionally. Exclusion criteria will be IQ < 85 [assessed by the Wechsler Intelligence Scale-V (WISC-V), 4 subtests: Similarities, Vocabulary, Matrix Reasoning, Block Design; 11–16 years [51]; > 16 years [52]], pubertas praecox vera [53], pregnancy, current glucocorticoid-containing medication, known genetic syndromes, history of traumatic brain injury, history of endocrinological disorder, any other chronic neurological disorder which influences the brain development and physiology, acute suicidal behavior and any current and history of psychiatric disorder according to DSM-IV and ICD-10 except mild depressive episode (ICD-10 F32.0) and moderate depressive episode (F32.1). Patients with mild and moderate depressive episodes were included because of the high comorbidity rate between anxiety disorders and depression [5]. Hormonal contraceptives and psychotropic medication will be noted and corrected for but are no exclusion criteria. The healthy control group will be matched according to sex, age, pubertal status and school education. For the control group, exclusion criteria additionally include current and history of in- and outpatient psychiatric and psychotherapeutic treatments and any current or lifetime psychiatric disorders.

### Procedure

After recruitment, participants and their legal guardians will be provided with written information on background, aim, study procedure, risks and advantages of participation, data collection and privacy policy (T0, see Fig. 1). After obtaining informed and written consent by the children and adolescents and their legal guardians, participants will be screened for eligibility with semi-structured diagnostic interviews (see Psychological Measures) (T1, see Fig. 1). In a second appointment, the assessment of salivary hormone concentrations under stress conditions will take place (T2, see Fig. 1). Each appointment will last approximately 2.5 h. The TSST [33] (T2b, see Fig. 1) will be conducted in order to induce a psychological and physiological stress response in children (see Physiological Measures). See Fig. 1 for an overview of the trial procedure.

**Fig. 1 Fig1:**
[figure not shown]
Schedule of Enrolment, Interventions and Assessments—Trial Procedure. *TSST* Trier Social Stress Test, *WISC-V* Wechsler Intelligence Scale for Children—V, *WAIS-IV* Wechsler Adult Intelligence Scale—Fourth Edition, *M.I.N.I-KID 6.0* Mini-international Neuropsychiatric Interview for children and adolescents, *SCARED-D* Screen for Child Anxiety Related Emotional Disorders—German Version, *SPAIK* Social Phobia and Anxiety Inventory for Children, *BAI* Beck Anxiety Inventory, *BDI-II* Beck Depression Inventory-II, *STAI* State-Trait Anxiety Inventory, *PDS* Pubertal Development Scale, *ECR-RC* Experiences in Close Relationships Scale—Revised Child version, *VAS* Visual Analogue Scale for perceived stress, anxiety, insecurity, tension, *OXT* Oxytocin, *CORT* Cortisol, *T2a* Time previous to TSST, *T2b* TSST, *T2c* Time after TSST

All children and adolescents will receive a 50 € gift voucher for participating. In case a participant and legal guardian withdraw their consent from participating at any given time, the data already obtained will be destroyed or only considered if written permission is obtained.

### Intervention

All participants will be exposed to an acute psychosocial laboratory stressor (TSST) while saliva samples will be taken. Participants with an anxiety disorder will receive in- and/or outpatient diagnostic/medical consultation/treatment (Treatment as usual, TAU) at the Clinic for Child and Adolescent Psychiatry, Psychosomatics and Psychotherapy, University of Regensburg. If the healthy controls show unexpected pathological psychiatric symptoms during the study procedure, they have access to detailed diagnostic/medical consultation/treatment options.

### Data assessment

#### Psychological measures

To determine eligibility criteria, semi-structured diagnostic interviews (see Table 1) will be conducted (T1, see Fig. 1). The German version of the Screen for Child Anxiety Related Emotional Disorders (SCARED-D) [50] will be used to screen the participants for anxiety disorders. The SCARED-D is a 41 item self-and parent-report questionnaire to identify children at the age of 9–18 in clinical samples while considering five different factors of main anxiety diagnoses (somatic/panic, general anxiety, separation anxiety, social phobia, school phobia) [49]. For detailed assessment of social anxiety and phobia according to the DSM-IV diagnostic criteria, the German Screening for Social Phobia and Anxiety Inventory for Children (SPAIK) [48] will be used. Here, 26 different situations representing psychological and physiological aspects of social phobia are presented to the child. The responder has to rate the frequency of occurrence of these situations on a three-point Likert-scale: 0 = never or hardly ever, 1 = sometimes, 2 = almost always or always [54]. The intensity of anxiety disorders according to the DSM-IV criteria will be assessed using the Beck Anxiety Inventory (BAI) [45]. Participants have to evaluate 21 statements according to how much they are bothered by the symptoms of anxiety experienced in the last seven days [55]. A total of 13 items assesses physical aspects of anxiety, five cognitive aspects and three relate to both.

**Table 1 Tab1:** Applied measures

Measure	Duration min	Number of items	Timepoint	Information
SCARED-D	15	41	T1	Screen for Child Anxiety Related Emotional Disorders (SCARED)—German Version
SPAIK	15	26	T1	*Sozialphobie und -angstinventar für Kinder* (Social Phobia and Anxiety Inventory for Children)
BAI	10	21	T1	Beck Anxiety Inventory
BDI-II	10	21	T1	Beck Depression Inventory-II
STAI	10	40	T1	State-Trait Anxiety Inventory for adults (STAI)
M.I.N.I.- KID 6.0	45		T1	Mini-international Neuropsychiatric Interview for Children and Adolescents (M.I.N.I.-KID)
ECR-RC	10	12	T1	Short version of the Experiences in Close Relationships Scale—Revised Child version
PDS	5	6	T1	Pubertal Development Scale
VAS	2		T2	Visual Analogue Scale for perceived stress, anxiety, insecurity and tension
WISC-V/ WAIS-IV	20		T1	Wechsler Intelligence Scale for Children—V / Wechsler Adult Intelligence Scale—Fourth Edition; 4 subtests (Similarities, Vocabulary, Matrix Reasoning, Block Design)

The State-Trait-Anxiety-Inventory (STAI) is a self-report instrument based on the differentiation between the presence and severity of temporary anxiety symptoms (State-Anxiety) and the longstanding generalized Trait-Anxiety as a stable personality trait [47, 56]. The STAI consist of two scales containing 20 items each with one scale addressing Trait- and another scale State-Anxiety.

The German version [46] of the Beck Depression Inventory-II (BDI-II) is a widely used self-report 21-item questionnaire for adolescents and adults from the age of 13 years. It is used to investigate the intensity of depression. Each item describes a particular symptom of depression with a list of four statements arranged in increasing severity. The responder has to choose one statement that best represents his/her feelings in the last two weeks [46]. Since the applicability of item 21 (loss of interest in sex) is limited for younger study participants, we excluded this item in our assessment.

Comorbidities will be assessed using the German Version of the Mini-international Neuropsychiatric Interview for Children and Adolescents (M.I.N.I.-KID 6.0) [44]. The M.I.N.I.-KID is a structured clinical diagnostic interview for DSM-IV and ICD-10 psychiatric disorders for children aged 6–17 years. As the version for adults, the M.I.N.I.-KID is organized in diagnostic sections (A–X). Each chapter contains Yes–No-questions grouped for each disorder in a language that is easy for children to understand [44]. Due to the high correlation between OXT release and the quality of attachment to parents and primary attachment figures, we measure attachment anxiety and avoidance with the German [57] short version of the Experiences in Close Relationships Scale-Revised Child version (ECR-RC) [58] for use in middle childhood and early adolescents. The ECR-RC is a self-report questionnaire on parent–child attachment containing two scales, each with 12 statements about the participant`s father or mother. Six statements rated from 1 (not at all) to 7 (very much) tap into attachment avoidance and 6 statements into attachment anxiety [58]. See Table 1 for an overview of the applied measures.

### Physiological measures and stress challenge

To minimize the effects of hormone fluctuations caused by the circadian rhythm [32], all participants will start the 2.5 h experimental test session (T2, see Fig. 1) at the same time in the afternoon (4:00 pm). Females who have begun menstruation will be tested in the luteal phase (time after ovulation) of their menstrual cycle, since the CORT stress response of females is more similar to the male reaction in the luteal phase than in the follicular phase [32, 59]. The onset of the female participants' ovulation and the pubertal development will be assessed using the German adaptation [60] of the self-report Pubertal Development Scale [61]. However, in previous studies, no main effect of sex for OXT levels in adolescents was found [32, 62]. Still, to minimize the effect of age and pubertal development [62, 63] both groups will be matched according to pubertal status [61].

At the end of T1, participants and their parents/legal guardians will be instructed to take one saliva sample by themselves at home within a relaxing atmosphere (T2a) and at least one hour after their last food intake. They will be asked to take the sample two days in advance of T2 in the afternoon, at the same time as the experimental test session (T2) takes place (4:00 pm). This will constitute the baseline salivary OXT and CORT level before the experimental test procedure (T2) will be conducted. The experiment will start with a 60 min relaxation period (T2a) to minimize external effects caused by previous food/drink intake, smoking cigarettes or stressful situations. During the experiment, participants will only be allowed to drink water [32]. Participants will be situated in a separate room (Room A) with relaxing material (reading, painting, puzzle, music). After 1 h (− 1 min before TSST start), the first salivary OXT and CORT level will be measured.

The TSST (T2b) will be conducted in room B in front of an unknown audience comprising two auditors and one experimenter (for more details see Kirschbaum et al. [33]). Participants will be introduced to the audience and informed about the upcoming task [42]. All participants have to give a free speech (5 min) for a mock job interview (application for a position as a student representative), for which he/she has 5 min to prepare. It will be feigned that this speech will be filmed and voice recorded [64]. Participants will be elucidated after the completion of the experiment. The second task will be an age-adapted mental arithmetic task (5 min), in which the participants will be asked to serially subtract a fixed number from a given starting number [42]. If the wrong number is calculated, the participant is asked to start the task from the beginning.

Upon completion of the TSST, participants will be seated in room A, thereby ending the stressful situation (T2c). To investigate the individual progression of coping with stress of each participant, no relaxing materials will be provided. Saliva samples will be taken at + 1, 5, 10, 20, 40 and 60 min after completing the tasks using Salivette^®^ (Sarstedt, Germany) collection devices and stored at − 20 °C until biochemical analysis. Salivary CORT will be measured at the laboratory of the Department of Biopsychology, Technical University of Dresden, Germany. Salivary OXT will be quantified by radioimmunoassay (RIAgnosis, Sinzing, Germany). In order to monitor the stress reaction during the procedure, heart rate will be recorded by an Ecg Sensor (EcgMove4, movisens, Germany) fixed with adhesive electrodes at the chest of each participant. Simultaneously to the physiological assessments, subjective levels of perceived stress, anxiety, insecurity and tension will be investigated using the Visual Analogue Scale (VAS) (Scale from 0 = feeling not stressed/anxious/insecure/tense at all to 100 = feeling highly stressed/anxious/insecure/tense, for more details see Hellhammer and Schubert, 2012 [37]) at 9 different time points [32]. In the relaxation period after the TSST, the experimenter will provide participants with positive feedback on their performance and the information that no video recording was made [32]. Finally, a clinical psychologist or doctor in charge will be available to talk in detail with the study participants and their legal guardians about the test procedure. He will also be available for advice/counseling if needed. See Fig. 2 for an overview of the test procedure.

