### Power calculation

An a-priori power calculation was conducted using G*Power 3 [65] assuming a level of significance of *p *< 0.05, an effect size of f = 0.4 and two groups. The effect size of f = 0.4 was based on the study published by Bernhard et al. [32] and determined from the effect of TSST on CORT and OXT. The power analysis—when considering a correlation between CORT and OXT (as found by Bernhard et al. [32])—was conducted for a rmMANOVA (repeated measures Multivariate Analysis of Variance) and considered 8 measurements of CORT and OXT. Here, a sample size of 30 was estimated to achieve sufficient power of 80%. In case of no correlation between CORT and OXT, an rmANOVA (repeated measures Analysis of Variance) will be performed. Power analysis revealed that here a sample size of 8 will be required to achieve sufficient power of 80%. To determine the effects of group and sex on basal OXT and OXT increase through an additional MANOVA, a power analysis with an estimated effect size of f = 0.25 (medium sized effect) determined a total sample size of 64 (32 participants in each group). The latter sample size was chosen.

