### Statistical analysis

To ensure objectivity the data will be assessed in accordance with the current standards of empirical research. The collected data will be evaluated using SPSS 25.0 (IBM Corp. Released 2017. IBM SPSS Statistics for Windows, Version 25.0. Armonk, NY: IBM Corp.). Using $$x^{2}$$—test for discrete analysis of variance (ANOVA) for continuous variables with group and gender as inter-subject factors, the demographic and psychometric data will be evaluated. The measured OXT and CORT levels will be transformed to achieve normal distribution. Correlations between psychological VAS ratings and OXT and CORT will be explored through Pearson correlations in case of normally distributed data and through Kendall’s τ otherwise. As correlation between OXT and CORT is expected, a rmMANOVA (repeated measures Multivariate Analysis of Variance) will be conducted to test the effects of time as a within-subject factor and group as a between-subject factor on OXT and CORT reactivity. In case of correlation between OXT, CORT and VAS ratings, VAS ratings will be included into the rmMANOVA, otherwise separate ANOVAs with the between-subject factor group and within-subject factor time will be conducted. In case of significant main effects or interactions, False Discovery Rate (FDR) [66] corrected post-hoc tests will be performed. Exploratory post-hoc analyses with FDR corrected p-values testing for effects of sex and age on OXT and CORT reactivity will also be conducted.

OXT and CORT increase will be calculated through area under the curve (AUC) analyses as described in Pruessner et al. [67]. Additionally, delta scores will be computed between the OXT and CORT baseline measure and the highest value for a measure of increase [68, 69] and between the highest OXT and CORT value and the lowest value after stress for a measure of recovery [70]. To determine group differences between OXT and CORT baseline, increase and recovery, MANOVAs will be computed with group as a between-subject factor and sex as a within-subject factor. In exploratory analyses, anxiety and depressive symptomatology scores will be included as covariates. As previous research has identified an effect of contraceptives on OXT baseline levels [38] a separate analysis will be run on female participants.

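### As written, stress-induced increase runs from a home sample taken two days earlier, so the increase score adds a home-to-laboratory shift to the TSST response

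*Protocol article*

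**What the plan says.** The protocol article, under Physiological measures and stress challenge, has participants collect one saliva sample themselves at home: "They will be asked to take the sample two days in advance of T2 in the afternoon", at 4:00 pm. It then states: "This will constitute the baseline salivary OXT and CORT level before the experimental test procedure (T2) will be conducted".

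The session itself starts at 4:00 pm with 60 minutes of rest in the laboratory. "After 1 h (− 1 min before TSST start), the first salivary OXT and CORT level will be measured". This sample is not called a baseline. The post-stress schedule is: "Saliva samples will be taken at + 1, 5, 10, 20, 40 and 60 min after completing the tasks". The label T2a is attached both to the home collection and to the laboratory rest period.

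Under Statistical analysis, "delta scores will be computed between the OXT and CORT baseline measure and the highest value for a measure of increase". The resulting increase scores enter the group MANOVAs and, if OXT and CORT correlate, both regression models. The Power calculation section "considered 8 measurements of CORT and OXT". The Discussion again lists the baseline sample separately from the frequent saliva samples. No sentence makes the sample at -1 minute the reference for increase.

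**The concern.** The second primary question asks whether patients and controls differ in their OXT change in response to the TSST. A score that starts at home two days earlier also contains the change of setting, day-to-day variation, collection at home without study staff, and anticipation of the visit. None of these is a response to the TSST.

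The groups are defined by anxiety, and the included diagnoses cover social phobia, agoraphobia and separation anxiety. It is plausible that coming to the clinic affects patients differently from controls. Matching on sex, age, pubertal status and school education does not remove that. A differential shift could create a group difference in increase, or hide a real one if it runs the other way. The same score feeds the analyses relating OXT increase to CORT increase, so the third primary question is touched as well.

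In addition, the highest value is not restricted to samples after the TSST. A participant whose level is highest on arrival could have that pre-stress value counted as the stress peak.

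**Working it through.** **1. Count of measurements.** Home 1 + pre-TSST 1 + post-TSST 6 = 8. The session alone gives 1 + 6 = 7. On the samples listed, the stated 8 is reached only by counting the home sample, so home is also a level of the time factor.

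**2. What the increase score contains.** Let H be the home sample, P the sample at -1 minute and M the highest post-TSST value. Then

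M - H = (M - P) + (P - H).

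Only the first bracket is response to the TSST. If P - H differs between groups by δ, the group difference in M - H is the difference in TSST response plus δ.

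**3. False-positive rate of the increase test.** From the protocol: 32 per group, alpha 0.05 (taken as two-sided). Assumed, because the protocol gives no values: SD 1 at each sample, correlation 0.8 among session samples and 0.5 between home and session, identical TSST response in both groups, and all session samples in one group shifted by δ.

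Hand approximation with the peak at a fixed time: SD(M - H) = √[2(1 - 0.5)] = 1, and SE = 1 × √(2/32) = 0.25.

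| δ (SD) | δ/SE | Rejection, hand | Rejection, simulated, highest of the post-TSST samples |
|---|---|---|---|
| 0.2 | 0.8 | 12.3% | about 13% |
| 0.3 | 1.2 | 22.4% | about 24% |
| 0.5 | 2.0 | 51.6% | about 55% |

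Taking the highest of several samples narrows the spread slightly, hence the somewhat higher simulated figures. With P as reference, δ cancels and the rate stays at 5%. With δ = 0 the home-based test is also at 5%.

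Varying the home-to-peak correlation from 0.3 to 0.7 in the hand formula gives 10-18%, 17-34% and 39-73% for the three shifts.

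**4. Group × time test with eight levels.** Under the same assumptions, the variance of (session mean - home) is 1 + (1 + 6 × 0.8)/7 - 2 × 0.5 = 0.829. The noncentrality is (32/2) × δ²/0.829, which is 0.77, 1.74 and 4.83. On F with 7 and 56 degrees of freedom, rejection is 7.6%, 11.5% and 26.9%. Simulation gives about 8%, 12% and 27%. With the seven session levels it is 5%.

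**5. Precision.** For a true group difference of 0.8 SD of the (M - P) change, power from P is Φ(0.8/0.25 - 1.96) = 89%. From H it is Φ(0.8 × √[(1 - r_P)/(1 - r_H)]/0.25 - 1.96), where r_P and r_H are the correlations of P and H with the peak. For example, r_P = 0.7 and r_H = 0.5 give Φ(2.48 - 1.96) = 70%, and r_P = 0.8 and r_H = 0.4 give Φ(1.85 - 1.96) = 46%. If r_P = r_H, nothing is lost.

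**The case against.** The Statistical analysis section does not say in one sentence that its baseline measure is the home sample. The link is the natural reading of two sections, and the figure of measurement time points was not available to check it. Ratings on the visual analogue scale are planned at 9 time points alongside the physiological measures, which the listed samples do not explain, so the count of 8 is supporting evidence rather than proof. Even so, the home sample is the only one the protocol names as baseline, and nothing points to the sample at -1 minute.

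The second primary question does not rest on the delta score alone. The repeated-measures MANOVA includes the home sample but is not anchored on it, and post-hoc contrasts could separate arrival from stress response. Recovery does not use the baseline. This narrows the point to the increase scores and, more weakly, the eight-level interaction test.

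A relaxed home reference also has a rationale. The sample at -1 minute may already contain anticipation, and subtracting it removes that part of the response. The 5% figure for the pre-TSST reference follows from assuming one shift common to all session samples. It does not show that reference to be free of anticipation. This stands, and it is why the home-to-pre-TSST change should be reported as well.

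Three stronger readings are not supported. A reader might infer that the two-day gap dominates the AUC, but the protocol states neither the AUC's reference sample nor its time axis. A reader might blame the clock-time offset (home at 4:00 pm, pre-TSST sample about an hour later), but both groups share it, so it largely cancels between them. It would also be tempting to move the home sampling time. Recruitment began in January 2020, and a change now would mix two clock times in the basal measure of the first primary question.

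**Conclusion.** The point holds for the increase score. As defined, it adds a home-to-laboratory shift to the TSST response, and a group difference in it cannot be attributed to the TSST. That follows from the definitions alone.

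How much it matters depends on a differential shift and on correlations that the protocol does not give. Under the stated assumptions, false-positive rates run from about 13% (0.2 SD) to about 55% (0.5 SD) for the delta score and from about 8% to about 27% for the eight-level group × time test. They are nominal if the groups shift equally. The loss of power is likewise conditional on the home sample correlating less with the peak than the pre-TSST sample does. A reader might infer that the stress-response result will be wrong. The documents support only that it would not be interpretable as a TSST effect without the pre-TSST reference. The home sample remains suitable for the basal-level question.

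**What to change.** - Define the delta score as the highest post-TSST value minus the sample at -1 minute.
- Compute any AUC from -1 to +60 minutes with the same reference.
- Run the repeated-measures reactivity model on the seven session samples, and restate the 8 measurements in the power calculation to match. The 64 participants come from a separate calculation on basal OXT and OXT increase that does not cite the number of samples.
- Keep the home sample, at its present time, for the first primary question.
- Report the home-to-pre-TSST change by group as a separate anticipation contrast, and the home-referenced delta as a sensitivity analysis.
- Give the home collection and the laboratory rest period different labels.

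The cost is wording in the analysis and power sections, and every sample needed is already scheduled. The small downside is that the sample at -1 minute may contain some anticipation, which the separate contrast makes visible.
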